### Strategies to improve adherence to interventions

Intervention sessions will be delivered according to adapted manuals and the intervention adherence will be monitored by number of sessions attended. The intervention will be delivered by trained therapist in supervision of senior therapist who have training and experience in conducting psychological interventions for SUD.

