### Data collection method

All participants (intervention and TAU groups) will undergo assessments at baseline, 3rd month (end of intervention) and at 6th month after randomisation. Participants will complete a self- report demographic information sheet (only at baseline) that will collect information related to age, duration of substance misuse, type of substance used etc., the MAP [47], SWEMWBS [42], EuroQoL (EQ-5D) [43] and CSRI [44]. All the assessments will be carried out by trained research assistants at baseline, 3rd month (end of intervention) and at 6th month.

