#### Statistical methods to handle missing data

The groups will be analysed on an intention to treat basis. The analysis will determine effect sizes to conduct power calculations for a larger trial. In accordance with the intention to treat principles, our aim is to follow-up all participants regardless of whether they have been lost during the intervention. Any missing follow-up data will be modelled on the assumption that it is missing at random. Logistic regression will be used to test this assumption, and to calculate probability of providing complete outcome data with baseline variables as predictors. These analyses will be used to create inverse probability sampling weights for subsequent analyses on outcome.

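### The dropout weights use baseline variables only, which is narrower than the missing-at-random assumption stated beside them, so week-24 secondary estimates can be biased

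*Protocol article*

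**What the plan says.** The section Statistical methods to handle missing data states the assumption first: "Any missing follow-up data will be modelled on the assumption that it is missing at random". It then names the method, a logistic regression used "to calculate probability of providing complete outcome data with baseline variables as predictors", and its purpose: "These analyses will be used to create inverse probability sampling weights for subsequent analyses on outcome". The same section gives the use of the results: "The analysis will determine effect sizes to conduct power calculations for a larger trial".

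Two other sections show what is observed after baseline. Under Data collection method, everyone "will undergo assessments at baseline, 3rd month (end of intervention) and at 6th month after randomisation" (weeks 12 and 24 in the abstract). Under Strategies to improve adherence to interventions, "the intervention adherence will be monitored by number of sessions attended". Neither the 3-month scores nor attendance is named as a predictor of the weights.

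**The concern.** The stated assumption and the stated method do not match. Missing at random lets the chance of being missing depend on anything observed. Inverse probability weights correct only for what is in the model that produces them. With baseline predictors alone, the weighted week-24 analysis further assumes that, among people alike at baseline, loss after week 12 is unrelated to how they were doing at week 12.

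The document gives some reason to doubt that. Participants enter after detoxification. The retention section attributes difficulty in keeping participants to the nature of the disorder. It also gives the treatment-as-usual (TAU) arm weekly contact calls for three months, so the contact schedule differs by arm.

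At stake are the between-arm estimates for the secondary scales and the effect sizes passed to the power calculation for a larger trial. The recruitment, retention, attendance, adherence and completion criteria do not use these weights.

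**Working it through.** The plan gives no figure for the weighting, so there is none to reproduce. The check is whether baseline-only weights recover a known difference under dropout patterns that the stated assumption permits.

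**Inputs from the protocol.** Overall loss of 30% (Sample size), hence 70% retained; 260 randomised, 65 per arm, 130 per factorial margin (Sample size, Table 2); follow-up at weeks 12 and 24.

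**Assumed inputs** (the protocol gives none). Two groups coded a = 0 or 1; one standard normal baseline covariate x; e1 and e2 independent standard normal.
- Week 12: y12 = 0.5x + √0.75·e1 + 0.5a.
- Week 24: y24 = 0.2x + 0.6·y12 + 0.65·e2 + 0.2a.
- True week-24 difference: 0.6 × 0.5 + 0.2 = 0.5. Within-group variance: (0.2 + 0.3)² + 0.36 × 0.75 + 0.65² = 0.94, so the SD is about 0.97.
- Everyone is seen at week 12; only week 24 is missing.

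**Log-odds of being retained**, with the intercept c set to give 70%:
1. Baseline only: c + 0.8x
2. Baseline and arm: c + 0.8x + 0.8(a − 0.5)
3. Week-12 outcome alike in both groups: c + 0.3x + (y12 − 0.25)
4. Week-12 outcome in one group only: c + 0.3x + 1.2a(y12 − 0.5)
5. Baseline, opposite direction by arm: c + 0.8x(2a − 1)

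**Bias in the week-24 difference, large samples.** The full weights use x, a, y12, x·a and y12·a.

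| Pattern | No weights | Baseline-only | Full |
|---|---|---|---|
| 1 | 0.00 | 0.00 | 0.00 |
| 2 | −0.048 | −0.056 | 0.00 |
| 3 | −0.054 | −0.058 | 0.00 |
| 4 | +0.200 | +0.220 | 0.00 |
| 5 | +0.215 | +0.215 | 0.00 |

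Relative size: 0.056/0.5 = 11%; 0.058/0.5 = 12%; 0.215/0.5 = 43%; 0.220/0.5 = 44%. In patterns 2 to 5 baseline-only weighting did no better for the difference than no weighting.

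**Against sampling error.** With 260 people (130 per group, 1,500 repeats) the SD of the baseline-only estimate was 0.146 to 0.157. For two arms of 65, multiply by √2:
- Pattern 3: 0.146 × 1.414 = 0.206; bias/SD = 0.058/0.206 = 0.28.
- Pattern 4: 0.150 × 1.414 = 0.212; bias/SD = 0.220/0.212 = 1.04. The 95% half-width is 1.96 × 0.212 = 0.42, so the bias is about half of it (0.220/0.42 = 0.52).

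**Total error at 130 per group**, √(bias² + SD²), baseline-only against full:
- Pattern 3: √(0.054² + 0.146²) = 0.156 against √(0.005² + 0.162²) = 0.162. No gain.
- Pattern 4: √(0.216² + 0.150²) = 0.263 against √(0.006² + 0.155²) = 0.155. A clear gain.

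**Effect on the next trial.** Required size varies as 1/difference² if all else is unchanged. Planning on 0.5 + 0.22 = 0.72 gives (0.5/0.72)² = 0.48 of the size needed. Planning on 0.5 − 0.058 = 0.442 gives (0.5/0.442)² = 1.28 times that size.

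**The case against.** The strongest reply is that this is a feasibility trial with a largely descriptive analysis. The affected results are secondary, a full analysis plan is still to come, and at 65 per arm random error outweighs the bias under mild dropout patterns. Much of that stands. In pattern 3 the richer weights bring no gain in total error, and the large figures need dropout that differs in direction or strength by arm, for which the document offers no data. The deferral to a later plan does not answer the point, because the predictors are already named here and a plan that follows this text would inherit them.

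Three stronger readings are tempting and are not supported.
- That week-24 results will be biased. Nothing in the document shows that dropout depends on arm, attendance or week-12 state, and the bias is zero if it depends only on the modelled baseline variables.
- That allocated arm is excluded from the weights. It is neither listed nor ruled out. Week-12 scores, however, cannot be baseline variables.
- That people seen at week 12 but not at week 24 lose their week-12 data. This follows only if complete means every visit; it may mean complete for the outcome and visit being analysed. The text does not settle it.

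**Conclusion.** The point holds in conditional form. The protocol fixes a weight model that is valid under a narrower assumption than the one it states, while collecting the data that would close the gap. Under the assumed patterns the bias in the arm difference runs from zero to about 44% of a true difference of 0.5. For a two-arm contrast at 65 per arm, that is small beside sampling error in the milder patterns and about one standard error in the strongest. These sizes rest on assumed coefficients, 70% retention and full attendance at week 12; week-12 data cannot help for anyone lost before then. The case for change is that the effect estimates are meant for a power calculation and that the correction is cheap. It is a change that should be made, and it does not threaten the feasibility conclusions.

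**What to change.** Define the weights separately for each visit, and say what counts as complete at that visit, so that week-12 data are kept for people missing at week 24.
- **Week-12 model:** baseline variables, arm and baseline-by-arm terms.
- **Week-24 model, for those seen at week 12:** the same terms plus the observed week-12 outcome and its interaction with arm. The week-24 weight is then the inverse of the product of the two probabilities. State how people who miss week 12 but return at week 24 are handled.
- **Attendance:** only as a term within the three active arms, since TAU alone has no study sessions.

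Alternatively, for continuous scores, fit one mixed model of weeks 12 and 24 to all available assessments. That uses the week-12 score without weights, though not attendance.

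The cost is wording in an analysis plan still to be written; no new data are needed. The downside is somewhat more variable weights (in pattern 3 the SD rose from 0.146 to 0.162), which can be limited by truncation under a rule set in advance.

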### Ethical considerations

Ethical approval for the study has been obtained from National Bioethics Committee (NBC) of Pakistan (Ref: No. 4–87/NBC-467/20/47-Amend/21/1240). RAs will ask eligible participants to provide written informed consent for participation. Those participants who are not able to read and write will be provided with verbal information (in local language) that will encompass all the points mentioned in the written informed consent in presence of an independent trusted member who can read and write chosen by the participant. The consent form will then be thumb printed by the participants along with signatures of the legal representative chosen.

### Protocol amendments

Any amendments to the protocol will be communicated to NBC and other relevant authorities. The trial registration will be updated accordingly and revised protocol will be shared with research team and study investigators.

### Oversight and data monitoring

The research team will meet every month to monitor progress and decide on operative issues related to the project. The trial manager will be responsible to oversee co-ordination between study centres. An independently chaired TSC and Data Monitoring and Ethics Committee (DMEC) will oversee the trial throughout its various stages. This will be independent of the trial management team. TSC will meet every 6 months or with advice from the chair as needed between meetings. The DMEC will monitor the data and ethical aspects throughout the trial and advise the TSC on changes to the conduct of the study and whether there are any ethical or safety reasons why the trial should not continue. DMEC will consists of three independent members that collectively have expertise on mental health, statistics and health services research.

### Risk management: adverse event reporting and harms

Where a Serious Adverse Events (SAE), or Adverse Events (AE) occur for a particular participant, the research team will halt the study for that individual and review: (a) whether to withdraw the participant from the study, and (b) whether to halt the entire project. AEs will be recorded throughout the trial and any AE occurred will be immediately reported to PI within 24 h. This decision will be based on a consideration of the likelihood that the study itself (including the therapy and assessment procedures) contributed to the SAE (thus making it an Adverse Reaction; AR). Information will be gathered including the participant’s and researcher or therapist’s perspective, and the timing of the AE or SAE (e.g. did it occur immediately after a intervention session?) to help inform this review. Where an AR is identified, it will be considered whether this could apply to other participants and therefore if the study as a whole should be halted. This review process will be documented. Adverse Events (AE) are defined here as any untoward, time-limited, worsening in participants’ mental state or leading to a persistent increase in disability or incapacity. The occurrence of AEs will be monitored by the DMEC.

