### Phase 3: feasibility factorial RCT

The feasibility of the intervention will be assessed using a factorial RCT, for MICBT and MBRP intervention, comparing four groups: (1) MICBT plus treatment as usual group (TAU), (2) MBRP plus TAU group, (3) the integrated MICBT and MBRP with TAU and (4) TAU group alone. In Pakistani culture, people consider themselves more as part of a family and larger community rather than as individuals. Therefore, a group approach is more culturally appropriate but for certain private/family issues the flexibility of some individual time with the therapists will be offered. The group sessions will consist of approximately eight participants.

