### Criteria for discontinuing or modifying allocated interventions

The study interventions outlined are not expected to cause any adverse effects nor there is any anticipated harm to come from study participation. However, participants will be free to withdraw from the study at any point. The intervention will be discontinued if any individual participant requests to withdraw from the study or if any adverse effects warrant terminating the intervention. Given that this is a feasibility study, there will be no modifications in allocated treatments but a process evaluation will be undertaken to refine the intervention for a future definitive trial. After completion of intervention session, participants in need of further clinical interventions or who have not responded to intervention and those in TAU group will be referred to appropriate services.

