#### Sample size

Based on the recommendations by Sim and Lewis [45], a minimum sample size of at least 50 participants per group is required for feasibility studies. Assuming 30% attrition rate, we aim to recruit a total of *N* = 260 participants, with 65 participants randomised to each arm according to 2 × 2 factorial design scheduled in given Table 2.

**Table 2 Tab2:** 2 × 2 Factorial design schedule of intervention with sample size

	TAU	MBRP	Total
MICBT	65	65	130
TAU	65	65	130
Total	130	130	260

The findings of this feasibility study will help determine the initial data for the outcome measures and will help in providing a sample size estimate for a larger future definitive trial; therefore, no formal power calculations have been undertaken.

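### Any adverse event halts the whole study for the participant, assessments included, which does not fit the intention-to-treat aim of following everyone up

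*Protocol article*

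**What the plan says.** The section on risk management, adverse event reporting and harms sets one rule for AEs and SAEs alike: "the research team will halt the study for that individual and review: (a) whether to withdraw the participant from the study". The second question for the review is whether the whole project should stop. An AE includes "any untoward, time-limited, worsening in" the participant's mental state. The decision rests on how likely it is that "the study itself (including the therapy and assessment procedures) contributed to the SAE (thus making it an Adverse Reaction; AR".

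The section on discontinuing or modifying interventions has a narrower rule: the intervention, not the study, stops "if any adverse effects warrant terminating the intervention". It does not say whether assessments then continue. It also states: "The study interventions outlined are not expected to cause any adverse effects".

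The section on missing data commits to intention to treat, aims to follow up everyone including those lost during the intervention, assumes follow-up data are missing at random, and builds inverse probability weights from baseline predictors.

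The last two arms are "3) the integrated MICBT and MBRP with TAU and (4) TAU group alone", "with 65 participants randomised to each arm". All participants "will undergo assessments at baseline, 3rd month (end of intervention) and at 6th month after randomisation". Progression requires, among other things, more than 70% retention, less than 30% attrition and more than 70% assessment completion.

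**The concern.** The harms section pauses the study, where intention to treat calls for pausing only the treatment. Three features make this more than loose wording.

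- **Trigger.** Any AE is enough, and a time-limited worsening of mental state counts as one.
- **Scope.** The section itself counts assessment procedures as part of the study, so a therapy-only reading is strained. In the TAU-alone arm there is no study intervention to stop, so the rule can only stop assessments and study contacts.
- **Exit.** For the individual, the review names withdrawal from the study and nothing short of it.

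At stake is outcome data lost because a participant got worse. Worsening mental state lies close to what the MAP (psychological health) and the SWEMWBS measure, and it arises after baseline. Weights built from baseline predictors may not fully correct for such loss. It can also count against the retention, attrition and assessment-completion criteria, so exits caused by the protocol's own rule could look like poor feasibility. And a participant who had an adverse event could lose planned follow-up.

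**Working it through.** **The texts side by side**

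| Point | Harms section | Discontinuation section | Missing-data section |
|---|---|---|---|
| Trigger | any AE or SAE | adverse effects serious enough to warrant it, or a request to withdraw | not applicable |
| What stops | the study, for that person | the intervention | nothing: the aim is to follow up all |
| Outcome named for the individual | withdrawal from the study | intervention ended; follow-up not mentioned | follow-up continues after loss from the intervention |

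The harms section does not refer to the discontinuation section, so staff have two rules for overlapping situations.

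**TAU-alone share:** 65/260 = 25%. This is the share for whom a halt can only affect assessments and contacts. It is not an estimate of lost follow-up.

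**Size.** The document gives no AE rate, halt length or withdrawal share, and has no figure of its own to reproduce. The rates below are assumptions, apart from N = 260, the 24-week follow-up and the 30% attrition limit.

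*1. Temporary halts only.* Let p be the share with one event, at a time uniform over 24 weeks, with a halt of d weeks and no missed visit made up. The probability that the halt covers week 24 is d/24: 1/24 = 0.042 or 4/24 = 0.167. Expected loss = 260 × p × d/24.

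| p (participants) | d = 1 week | d = 4 weeks |
|---|---|---|
| 5% (13) | 0.5 | 2.2 |
| 10% (26) | 1.1 | 4.3 |
| 20% (52) | 2.2 | 8.7 |

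The largest is 8.67/260 = 3.3%. The expected loss at week 12 is the same.

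*2. Halts that end in withdrawal.* Let o be other attrition and a the event-related loss among those otherwise retained. Total attrition = 1 − (1 − o)(1 − a). It reaches 30% when a = 1 − 0.70/(1 − o). The lowest o, 5%, matches the 95% retention cited in the retention section.

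| o | a that reaches 30% | total at a = 5% | total at a = 10% | total at a = 20% |
|---|---|---|---|---|
| 5% | 26.3% (65/247) | 9.8% | 14.5% | 24.0% |
| 15% | 17.6% (39/221) | 19.3% | 23.5% | 32.0% |
| 20% | 12.5% (26/208) | 24.0% | 28.0% | 36.0% |
| 25% | 6.7% (13/195) | 28.8% | 32.5% | 40.0% |

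At a = 5% all four rows meet the criterion. At a = 10% only the last fails. At a = 20% only the first passes.

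**The case against.** The strongest reply is that there is no contradiction. The halt is provisional, withdrawal depends on whether the study contributed to the event, and nothing prevents resumption. The option to stop only the intervention exists in the discontinuation section, and the harms section does not claim that its list is complete. The follow-up commitment is an aim, which can coexist with a safety exception. Pausing assessments is a reasonable precaution when assessments are themselves a possible cause. The effect may be nil, and details such as halt length and visit windows are commonly left to the full protocol.

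Much of this stands. The conflict is a tension and not proof that data will be lost; a TAU-arm event would have to be linked to study procedures before withdrawal was indicated; and the absence of halt lengths or visit windows is no criticism of a condensed article.

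It does not dispose of the point. The article states a rule here, and that rule stops the study. There are only two follow-up visits, and a halt may cover one of them. The discontinuation section does not say that follow-up continues. The precaution can be kept for cases where the assessments are suspected, without applying it to every AE.

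**Conclusion.** The concern holds. The halt rule is broader in trigger and scope than the discontinuation rule and does not fit the stated follow-up aim. It should be corrected before recruitment.

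Its size cannot be determined from the document and may be zero. Temporary halts alone are a small matter under the assumed rates. Withdrawals would alter the progression decision only if they were common or other attrition was already near the limit. These figures rest on assumed event rates, halt lengths and attrition, on uniform event times, and on no missed visit being made up. The case for changing the text rests on the wording and on the outcome-related nature of the loss, not on a predicted number.

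**What to change.** In the harms section, replace the instruction to halt the study for the individual with the following:

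- After an AE or SAE, pause the intervention, where the participant is receiving one, until the review is complete.
- Allow the review to stop the intervention without ending study participation.
- In all arms, TAU alone included, carry on with the week-12 and week-24 assessments unless the participant withdraws consent for them, or they are suspected or found to have contributed to the event. In that case defer them until the review is complete.

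The safety review and the option to stop the whole project remain. The cost is a wording change in one section, a few more assessments of participants who had an event, and the routine notice to the ethics committee and registry update described under protocol amendments. The trial status section says recruitment has not begun, so on the document the change can precede any enrolment. Sessions missed during a pause are still missed, so attendance is unchanged.

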### Dissemination plans

Study findings will be published as widely as possible in peer reviewed and non-peer reviewed journals and will be presented at local participatory centres, and national and international conferences. Workshop and seminars will be organised in collaboration with established partnerships to disseminate research findings and also to increase awareness and reduce stigma associated with SUD. The study findings will also be disseminated through the PILL newsletter. We publish quarterly newsletters on various mental health problems which are circulated across Pakistan to primary care, secondary care, colleges, universities, community centres and to service users and families. Lay summaries will be made available on the project website and shared via social media sites, i.e. Facebook page, Instagram and twitter to make it available to the wider public. Press releases will be made relating to key project findings. Members of the research team may give interviews relating to the study to the media outlets. Presentations about the research and key findings will also be undertaken with stakeholders linked to the project including clinical services, clinicians and local communities. Furthermore, the overall dissemination will take place after having an adequate dissemination plan which include journal publications.

